### Screening and recruitment

The participating healthcare centers were selected because they have the most recent version of the Electronic Health Record System that allows linking clinical information to the mobile app and the information board used in this study. These centers count with the necessary health information system infrastructure. Each of these centers takes care of the clinical control of diabetes patients. The primary healthcare workers of the participating centers will screen their DM2 patient lists and will invite eligible patients. Patients will receive an invitation letter and a leaflet with general information about the study. Eligible patients may also be contacted by phone, emails, or text by the healthcare professionals. Patients will be enrolled for screening over a 9-month period (t −2). During the first visit of the screening phase (time point t −1; Table 1), the eligibility criteria and medical record will be revised by the healthcare professionals. In case the patient is potentially eligible, they will be invited to a HbA1c measurement to complete the second eligibility assessment (t −1). Once the diagnosis of uncontrolled DM2 has been made, the patient will be asked to sign a written consent. In the next phase (t 0) the participants will be randomly allocated to either the intervention or control group (t 0). At the same time, all other baseline measurements and laboratory tests will be conducted (t 0).

**Table 1 Tab1:**
[figure not shown]
The schedule of enrolment, interventions, and assessments in the SANENT trial

^1^time-points after randomization

### Inclusion and exclusion criteria

The inclusion and exclusion criteria for patient enrolment are presented in Table 2. Both men and women treated for DM2 with an HbA1c> 8.5% and ≥20 years of age are eligible to participate in the study. Eligible patients need to be signed up for diabetes treatment and control in one of the participating primary healthcare practices. Participants need to have access to a mobile phone or, alternatively, have a family member who will help them in sending, understanding, and retrieving messages and information provided in Spanish language through the mobile application.

**Table 2 Tab2:** Inclusion and exclusion criteria for patient enrolment

Inclusion criteria	
- Men and women with DM2 - Age at least 20 years old - HbA1c > 8.5% - Have access to a smartphone or have a family member over 18 years of age with a smartphone and will help in sending, understanding, and retrieving messages and information - Assigned for diabetes treatment and control to one of the participating primary healthcare centers - Sign informed consent to participate in the study	
**Exclusion criteria**	
- Pregnancy, within 3 months post-partum or planning pregnancy during the trial - Breastfeeding - Serious medical condition (i.e., dialysis) - Not be a permanent resident of the participating states	

Participants who are pregnant, within 3 months postpartum or planning pregnancy during the trial; are breastfeeding; have a serious medical condition that, in the opinion of the investigator, makes them ineligible (i.e., dialysis treatment); have been admitted to hospital within the last 3 months for hyperglycemia or hypoglycemia; or are not permanent residents of the states the study is conducted are not eligible to participate in the study.

### Random allocation

This trial will use a parallel-group design, randomizing patients to either the intervention or the control arm by a computer-generated sequence with an allocation ratio of 1:1. The randomization of the study participants will be done after having provided consent and when all baseline assessments have been completed to minimize reporting and selection bias.

Random allocation will be done using a validated secure web-based randomization operated by a data manager, not involved in the patient recruitment, located at the Universidad Nacional Autonoma de Mexico. This will ensure concealment of the treatment sequence up to the allocation. The treatment sequence will be generated by a computer-generated sequence of random numbers. The block randomization method will be used. Allocation will be carried out with an algorithm to ensure groups are balanced for important baseline prognostic and other factors: study site, age (< 65/≥65 years), sex (male/female), duration of diabetes (< 5 years/≥5 years) and number of medications (< 5/≥5) which are considered as a key prognostic variable for the primary outcome of this trial. The treatment allocation codes will be concealed in sequentially numbered envelopes that will be opened each time a patient will be enrolled.

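### The protocol gives two orders for baseline and allocation and two unlinked allocation mechanisms, in an open-label trial with self-reported baseline outcomes

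*Protocol article*

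**What the plan says.** On timing, Random allocation is explicit: "The randomization of the study participants will be done after having provided consent and when all baseline assessments have been completed". It gives the reason as limiting reporting and selection bias. Screening and recruitment describes a different sequence. The eligibility HbA1c and consent come first; then "In the next phase (t 0) the participants will be randomly allocated to either the intervention or control group (t 0"), and the next sentence reads "At the same time, all other baseline measurements and laboratory tests will be conducted (t 0").

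On mechanism, Random allocation says: "Random allocation will be done using a validated secure web-based randomization operated by a data manager, not involved in the patient recruitment". The sentence after it credits this arrangement with keeping the sequence concealed until allocation. The section then names block randomisation and an algorithm that balances five factors: study site, age, sex, diabetes duration and number of medications. It ends with "The treatment allocation codes will be concealed in sequentially numbered envelopes that will be opened each time a patient will be enrolled".

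Blinding states that neither patients nor primary care physicians can be masked to the arm. Only the laboratory staff who measure HbA1c and the statistician are masked.

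**The concern.** Completing baseline before the arm is known protects baseline data in an open-label trial. The protocol gives that reason itself, yet its recruitment section does not keep the order. A patient who already knows the arm may answer differently about quality of life, adherence, mood, diet or activity. A shift of that kind would enter any change from baseline.

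The second issue is concealment. The assurance given is tied to the web system. If numbered envelopes decide the arm in practice, that assurance describes a safeguard that is not in use. Whether envelopes are adequate then depends on custody and handling, on which the text is silent. Staff cannot follow both descriptions, and centres could resolve the conflict differently. Neither problem can be repaired after a patient has been allocated.

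**Working it through.** **Timing.**

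- Random allocation: consent, then all baseline assessments, then allocation.
- Screening and recruitment: record review and eligibility HbA1c (t −1), then consent, then allocation together with all other baseline measurements and laboratory tests (t 0).

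The first requires every baseline item to be finished before the arm is released. The second sets no order between allocation and every baseline item except the eligibility HbA1c, and it mentions allocation first.

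**Which outcomes are exposed.** The Outcomes section lists Morisky, SF-36, the ENSANUT diet questionnaire, the physical activity questionnaire and the Beck questionnaires at baseline and month 12. All are self-reported secondary outcomes. The eligibility HbA1c precedes allocation in both accounts, and HbA1c is measured by masked laboratory staff. The timing conflict therefore bears mainly on the secondary outcomes.

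**Mechanism.** There are three ways to read the web system and the envelopes together.

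1. The web system releases each arm. The envelopes then have no function.
2. The web system only generates the list, and envelopes carry it. Concealment then rests on the envelopes, not on the web system credited with it.
3. Envelopes are a back-up. They would then not be opened for every patient, as the text says they are.

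No reading leaves both statements true and useful as written.

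**Balance.** Inputs: 126 patients per state and 378 in total (Sample size calculations), 1440 in total (Trial design), four two-level factors plus site (Random allocation).

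The 126 reproduces. Per arm, n = 2 × (1.960 + 1.282)² × 1.5² / 1.0² ≈ 47.28, and 2 × 47.28 / 0.75 ≈ 126. Three states give 3 × 126 = 378.

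Cells per site = 2⁴ = 16. The number of sites is not given, so a range is shown:

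| Sites (assumed) | Cells | Patients per cell at 378 | Patients per cell at 1440 |
|---|---|---|---|
| 3 (site = state) | 48 | 7.9 | 30 |
| 15 | 240 | 1.6 | 6.0 |
| 30 | 480 | 0.8 | 3.0 |

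A simulation gives the mean absolute difference in numbers between arms within a level of the four patient factors. It used 378 patients and 300 runs. Assumed: blocks of 4, factor prevalences 0.3, 0.65, 0.6 and 0.4, and minimisation that assigns the favoured arm with probability 0.8.

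| Method | 3 sites | 15 sites |
|---|---|---|
| One blocked list per site | 7.6 | 7.6 |
| Separate blocked list per stratum | 3.6 | 7.4 |
| Central minimisation | 1.5 | 1.5 |

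Stratum-specific lists can be put in envelopes, and they help when sites are few. Minimisation depends on the patients already allocated, so it cannot be packed in advance. The protocol's unnamed algorithm could be either kind, and only one kind is compatible with envelopes.

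**The case against.** The best defence on timing is that Random allocation states a clear order and its reason, and that the recruitment section may mean only that everything happens at the same t 0 visit. The schedule in Table 1 is not available to settle this, and enrolment in the envelope sentence may mean the moment of randomisation. It is therefore not established that baseline questionnaires will be collected after the arm is known. That stands. What remains is that one section guarantees the order and the other does not.

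On envelopes, a reader might infer that centre staff who screen their own patient lists also hold them and could select patients. The documents do not say so. The only operator named is a data manager outside recruitment. Weaker concealment is a risk that depends on custody, not a demonstrated fault.

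A reader might also infer that five-factor balance cannot be achieved. The text does not support that. It speaks of numbered envelopes, not of one series, and separate blocked series per stratum fit the stated block method. Record review at t −1 means that the factor levels can be known in time to choose the right series. With three sites the simulation shows such sets improving balance (3.6 against 7.6).

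Block sizes and similar details are commonly left to the full protocol and are not criticised here.

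**Conclusion.** The point holds as two contradictions in the text: the order of baseline and allocation, and the mechanism that assigns the arm. The consequence is possible bias in self-reported baseline data, mainly affecting secondary outcomes, and a concealment assurance that does not clearly apply to the mechanism in use. The contradictions rest on the wording alone and need no assumption.

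No numerical bias is claimed. Its size would depend on how far knowledge of the arm shifts answers and on how baseline enters the analysis of each questionnaire, and the article gives neither. The cell counts and simulated differences show only that the choice of mechanism limits which balancing methods are possible. They rest on assumed site numbers, block size and prevalences, and on 378 patients, a total that itself differs from the 1440 stated elsewhere.

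**What to change.** 1. In Random allocation, delete the envelope sentence. Allocate only through the web system already planned, and have it release the arm after consent is recorded and the baseline form is complete.
2. In Screening and recruitment, reword so that all baseline measurements and laboratory sampling precede allocation.
3. In Random allocation, state one balancing method that the web system runs, and say whether study site means state or health centre. Stratified blocks and minimisation are both defensible; the choice is a trade-off that turns largely on the number of sites.

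The cost is protocol wording and a setting in a system that the trial already has. The small downside is that allocation waits for the baseline form.

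Trial status has recruitment ending on 12 April 2022, eight days after the article's publication date. For patients already allocated, the trial report should therefore say which mechanism and order were actually used.

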### Blinding

Because the SANENT trial is an open-label study, neither the primary healthcare physicians nor patients can be blinded to the patients’ allocation to either intervention or control arm. Thus, blinding will apply only for the study endpoints. To guarantee the blind assessment of the primary endpoint of the study (HbA1c reduction), the laboratory personnel involved in its measurement will be blinded to the patient’s allocated treatment strategy. Also, the statistician analyzing the data will be blinded in regard to the patients’ allocated groups.

### Interventions

Participants assigned to the intervention group will use a mobile application on their smart phones that will assist them with their diabetes control, provide and update information on their clinical history, offer a monitoring of their nutritional and physical activity habits as well as anthropometric measurements, provide recommendations how to improve on nutritional habits and physical activity behavior, and assist in planning and reminding on clinical appointments. The mobile health application was tested and evaluated in a pilot project in 31 DM2 patients as part of this project. Based on the feedback received, the mobile application was revised and finalized to be sued in this project.

The content and description of the patient mobile health application are presented in Table 3.

**Table 3 Tab3:** Description of the patients’ mobile health application.

Subject	Description of content
Patient profile	Patient’s personal information, as well as information regarding clinical history, laboratory measurements, and current pharmaceutical treatment.
My state of health	Information about age, body weight, height, body mass index, glucose, total cholesterol, triglycerides, blood pressure, and glycated hemoglobin (HbA1c).
My measurements	Information about serum glucose, blood pressure, heart rate, respiration frequency, and oxygen saturation.
My studies	Information is classified into three analysis sections. A) Health center laboratory; Serum glucose, total cholesterol, triglycerides, glycated hemoglobin (HbA1c), creatinine and urea. B) Alternate laboratory (Lab Salud Digna); Serum glucose, total cholesterol, HDL cholesterol, LDL cholesterol, triglycerides, HbA1c, serum creatinine, serum albumin and urea. C) Complementary studies: information about of ECG, check-ups to assess diabetes complications (retinopathy, nephropathy, neuropathy) study visits.
My medications	Record of pharmacological treatment with its doses.
My body	interactive module monitoring nutritional habits, physical activity, patients’ self-perceived mood, and taking care of my feet. This module also contains a section that allows the patient to view changes and trends in their anthropometric measurements.
My recommendations	Provides recommendations on healthy eating habits, physical activity, mental health, and taking care of my feet.
Medical appointment	Information on upcoming clinical appointments (clinical control, laboratory tests).
Contact	Interactive module allowing patients to provide questions and comments about the mobile application.

The participating physicians will have access to the patient’s information through a mobile information tablet. That specific tool will allow the physician to view and consult all patient information of the patient’s mobile application. It will use a Java programming language, having an exchange of information through the Apache Web Server and from the Tomcat Application Server in a Java environment inbuilt on the SQL Server manager. Thus, the participating physician will have direct access to all clinical information, visits, lifestyle changes, and cardio-metabolic control of the DM2 patient. The main idea is that the mobile information board will help the physician to monitor better the treatment and control of his patients.

Participants assigned to the control arm will continue their diabetes care without mobile health technology assistance. This comparer was chosen as it is the current standard of care in the Mexican primary healthcare system.

The duration of the intervention will be 12 months. Each patient will be invited to follow-up visits and measurements every 3 months (month 3, month 6, month 9, and month 12).

### Strategies to improve compliance to the intervention

The research team has developed several strategies to improve compliance during the intervention:
All study participants will be informed and reminded about all testing arrangements, intervention routines, benefits, and potential harms to make them fully understand the importance of their participation in the study.All study participants will perform the intervention routine under the supervision of qualified medical personnel.The study coordinator will maintain contact with all study participants throughout the study and remember them about all scheduled appointments. If an appointment will be missed, the trial coordination team will try to contact the study participant and assist with complying with the scheduled visits.

### Relevant concomitant care permitted or prohibited during the trial

The study participants will be asked not to take part in any other programs related with clinical control of their diabetes during the proposed trial. In addition, participants are prohibited from taking any other treatments as part of their routine medical care.

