A recent review showed that the use of mHealth technology in the clinical care of patients with DM2 can result in improved treatment outcomes [16]. They also highlighted that a mHealth intervention need not be restricted to shot messages (SMS) alone. Mobile health technologies have the capacity to grant fast access to information and aid in instant communication for patients with DM2 and healthcare professionals [17]. One third of the current studies were in North America and one third in Asia [18]. Only few studies included DM2 patients in South- America (5%). Moreover, the study setting varied a lot in previous studies with only a 24% of the scientific studies carried out in the primary care sector or specialized outpatient clinics (14%). The mobile health interventions used in previous international studies were also diverse in nature and utilized a wide range of technological innovations such as text messaging (SMS), mobile applications as well as secure websites/web-portals that could be accessed through the diabetes patients' mobile device [8]. Thus, more information is needed on the benefit of mobile health technologies in clinical care settings and whether combining different technological innovations may provide additional benefits.

Therefore, this trial will compare a diabetes management strategy using an information board and a mobile application versus standard care in patients with uncontrolled DM2 within the primary health care system in Mexico.

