### Outcomes

The primary endpoint of the study will be the change in HbA1C within the groups and the differences between the groups. HbA1c will be measured at baseline, 3-month, 6-month, 9-month, and 12-month follow-up visits in all participants. The primary time-points for HbA1C are the 6- and 12-month measurements (Table 1).

The secondary outcomes of the study include differences in the mean cholesterol, LDL cholesterol, HDL cholesterol, systolic and diastolic blood pressure, triglycerides, microalbuminuria, waist circumference, body mass index, and muscle mass index. The laboratory measurements will be performed at the beginning of the intervention and at month 12 (Table 1). The anthropometric measurements will be done every 3 months. In addition, secondary outcomes will be treatment compliance measured by the Morisky score [23], quality of life using the Short Form 36 Health Survey Questionnaire (SF-36) [24], nutritional habits assessed by the ENSANUT questionnaire [25], and physical activity by the international physical activity questionnaire [26]. In addition, anxiety and mental health will be evaluated using the Beck questionnaires [27, 28]. The questionnaires will be applied at baseline and at 12 months of the intervention (Table 1).

Finally, process indicators related to the use of mobile application and the information board (usage time and frequency, user satisfaction among others) will also be assessed.

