### Data analysis plan

All data collected locally at each enrolling unit will be recorded into an electronic database. Clinical data to be input into the database include demographic information, results on blood and urine laboratory tests performed in each center, ongoing treatment (dose and medication), as well as information on adverse events during follow-up of the trial. The quality of data obtained will be validated by expert personnel at each study site.

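### The concomitant-care rule bans undefined other treatments within routine care, which does not fit a comparator defined as standard care

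*Protocol article*

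**What the plan says.** The Protocol article, under Relevant concomitant care permitted or prohibited during the trial, gives two rules. The first asks participants to stay out of other programmes for diabetes control. The second, introduced as an addition to the first, says that "participants are prohibited from taking any other treatments as part of their routine medical care".

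The comparator is set in the Interventions section: "Participants assigned to the control arm will continue their diabetes care without mobile health technology assistance". The reason follows: "This comparer was chosen as it is the current standard of care in the Mexican primary healthcare system". The Background states the trial's aim in the same terms, as a comparison "versus standard care in patients with uncontrolled DM2 within the primary health care system in Mexico".

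The patients are described under Inclusion and exclusion criteria: "Both men and women treated for DM2 with an HbA1c> 8.5" per cent. Of the participating sites, Screening and recruitment says: "Each of these centers takes care of the clinical control of diabetes patients".

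**The concern.** The word *other* in the second rule has no stated reference point. No section lists permitted treatments or says whether doses may be changed or drugs added. The reader has to guess what is forbidden, and the natural guesses do not agree with a control arm that receives standard care.

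Two things are at stake. The first is the meaning of the comparison. If the rule were followed, the trial would compare the app and information board with restricted care, and the result could not be reported as a comparison with standard care. The second is patient care. Patients with poorly controlled diabetes could wait for treatment intensification that their physician thinks necessary.

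**Working it through.** This is mainly a matter of wording, so the check sets the sections side by side under each reading.

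**Reading 1: no routine treatment at all.** This contradicts the Interventions section, where controls continue their diabetes care. Other sections also make it implausible as an intention:
- Eligible patients are already on treatment for diabetes (Inclusion and exclusion criteria).
- Allocation is balanced on number of medications, below 5 or at least 5 (Random allocation).
- The app holds a record of drugs and doses (Interventions, Table 3).
- Treatment compliance is a secondary outcome (Outcomes).
- The database is to hold "ongoing treatment (dose and medication") (Data analysis plan).

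**Reading 2: nothing beyond the existing regimen.** Controls could keep their current drugs, so there is no flat contradiction, and changes of dose are not clearly barred. Additions are barred. Every participant enters with HbA1c above 8.5% despite being treated, and attends a centre responsible for diabetes control. A regimen that cannot be added to for a year does not fit a comparator called standard care. It also limits what the physician can do with the information board, whose stated purpose in the Interventions section is better monitoring of treatment and control.

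The sections that make Reading 1 implausible do not settle Reading 2. They show that existing medication was expected, but not whether additions were allowed.

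**Safeguards elsewhere.** The section on discontinuing or modifying the allocated intervention lets the principal investigator withdraw an unsuitable participant. Under Monitoring, the Data Monitoring Committee reviews adverse events. Neither allows a treatment to be added while the patient stays in the trial.

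**Scope.** The rule is addressed to all participants: 378 by Sample size calculations, 1440 by the Abstract and Trial design. The second sentence gives no period of its own. The section heading places it during the trial, so it is taken to run for the 12-month intervention. Under Outcomes, "HbA1c will be measured at baseline, 3-month, 6-month, 9-month, and 12-month follow-up visits in all participants".
- Follow-up results: months 3, 6, 9 and 12, so 4.
- Results that arrive before the intervention ends: months 3, 6 and 9, so 3 of 4.
- Primary time points within the period: months 6 and 12, so 2 of 2.

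**Sample size.** The stated 126 per state reproduces and does not depend on this rule. With a difference of 1.0%, SD 1.5%, two-sided alpha 0.05 and power 90%, n per arm = 2 × (1.5/1.0)² × (1.960 + 1.282)² ≈ 47.28. With 25% dropout, 2 × 47.28 / 0.75 = 126.1 per state. Rewording the rule changes none of these inputs. The document gives nothing from which to estimate how a treatment ban would shift HbA1c in either arm, so no effect on power is computed.

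**The case against.** The strongest counter-argument is a third reading: treatments other than those the participating centre itself provides. The preceding sentence bars other programmes, so *other* might mean outside the trial and the centre's own care. The sentence is also addressed to patients, and no section restricts what the physician may prescribe. On this reading there is no conflict with the comparator. It is conceivable, but it strains the text. The sentence places the forbidden treatments inside routine medical care, and it is presented as a further rule after outside programmes have already been excluded.

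Several other objections stand in part:
- That standard care at these centres includes adding drugs is an inference. It is a reasonable one for treated patients above 8.5%, but the article does not say so.
- The full protocol is not shown and may define permitted treatment. How sites applied the rule is therefore unknown, and delayed intensification is a possibility rather than an observed fact. The absence of a detailed escalation scheme from an article would be no fault. The point here is what the published sentence states.
- The visit counts measure how long the rule applies. They do not measure harm.
- The proposed wording chooses a policy although the intent is not stated. It is the choice that matches the declared comparator and the sections that presuppose ongoing medication.

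**Conclusion.** The concern holds. As written, the rule either contradicts the standard-care comparator (total ban) or fails to fit it (ban on additions). The one reading that would remove the conflict does not sit well with the sentence's own words, and no other section resolves the matter. The likeliest explanation is a drafting error, but the sentence is current text that governs patients' treatment, and it should be corrected.

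The rule reaches all participants in both arms for the 12-month intervention, including both primary time points. Because it applies equally to both arms, no differential bias is claimed. No numerical effect on HbA1c, power or sample size is claimed either. The conclusion rests on two assumptions: that the rule runs for the intervention period, and, for the second reading only, that standard care for these patients may include adding drugs.

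**What to change.** Replace the second sentence of the concomitant-care section with:

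> Routine diabetes and comorbidity treatment, including changes made by the treating physician, is permitted in both arms and recorded in the same way in both; only participation in other diabetes-control programmes is excluded.

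Notify sites by the route set out under Plans for communicating important protocol amendments to relevant parties.

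Two smaller steps would help readers judge which comparator was delivered. The first is to document how each site applied the rule until the change. The second is to tabulate treatment and dose changes by arm from the medication data named in the Data analysis plan, as far as the recording frequency allows, since the article does not state that frequency.

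The cost is a one-sentence amendment, one notice and query to sites, and one table from data the plan already collects.
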